## Abstract

**Introduction::**

Colorectal cancer has been ranked third among the most common cancers worldwide and raised to the second leading cause of cancer death with nearly one-tenth of cancer-related deaths globally, and nearly half of colorectal cancer patients present with or develop colorectal cancer liver metastasis (CRLM). Buzhong Tiaogan Formula (BTF) has been proven to treat CRLM in our team, but there are lacking of evidence on its effective in delaying colorectal liver metastasis (liver depression spleen deficiency type), so we will evaluate the efficacy and safety of BTF in preventing the occurrence of CRLM.

**Methods::**

This randomized controlled trial (RCT) will be carried out in 3 different hospitals in Shanxi Province planning to recruit 150 CRLM patients with the type of liver depression spleen deficiency. The control group will be treated by basic antitumor therapy and the treatment group will use BTF plus basic antitumor therapy. The primary outcomes will be quality of life of included patients, the time of occurrence of liver metastasis, the score of traditional Chinese medicine symptom for the type of liver depression spleen deficiency; and the secondary outcomes will include overall survival, progression-free survival, DFS, tumor microenvironment and immune state of the included patient. Safety evaluation will be recorded during the whole study. All data in this RCT will be analyzed by SPSS 23.0 software. This study has been approved by the Clinical Research Ethics Committee of Shanxi Province Hospital of Traditional Chinese medicine (2021Y-06016).

**Discussion::**

The results of this RCT will contribute to BTF for delaying colorectal liver metastasis (liver depression spleen deficient type). And the results from this RCT will be published in a relevant journal after finished.

**Trial registration::**

ChiMCTR2100005268 (September 4, 2021).

## Introduction

1

Colorectal cancer (CRC) has been ranked third among the most common cancers worldwide and has risen to the second leading cause of cancer death with nearly one-tenth of cancer-related deaths globally.^[1,2]^ According to the latest global cancer data from International Agency for Research on Cancer (IARC), the number of new cases of CRC in 2020 was about 1.93 million worldwide and the number of deaths was up to 930,000. In China, the incidence has been jumped the second among cancer with 55 million new cases annually, and the mortality has ranked fifth among common causes of cancer death, with 28 million new deaths in 2020.^[3]^ About 20% of patients with CRC have advanced disease at the time of diagnosis, and 35% of patients treated with curative intent will develop metastatic disease.^[4,5]^

Nearly half of CRC patients present with or developed colorectal cancer liver metastasis (CRLM).^[6]^ Unfortunately, approximately 25% of CRLM are deemed to be unresectable. Chemotherapy is considered as the best strategy, which offers the best chance of cure, improving 5-year survival rates from 40% to 50%.^[7–9]^ Significant advancements in the perioperative management of CRLM have led to the ability to effectively perform more complex surgeries, such as improved diagnostic modalities, multistage hepatectomies, portal-vein embolization, and downstaging with preoperative systemic therapy.^[10]^ Despite these advances, disease recurrence is common, occurring in 60% or more of patients.^[11,12]^ But because of multiple lesions, scattered distribution, tumor location, intolerance of patients, the patients are unable to withstand accept the surgical treatment. In this pessimistic situation, other therapies should be developed. Minimally invasive treatments are the chemical treatment of the hepatic artery embolization, chemical ablation, and a variety of melting temperatures. Radiation therapies are radiation physics, radiation biology, radiation treatment technology, and equipment. Chemical and molecular targeted therapies include monoclonal antibodies, gene therapy, and biotherapy. 5-fluorouracil (5-FU) is the main chemotherapy agent in the treatment of CRC, and other drugs contain capecitabine, ticio, oxaliplatin, irinotecan. In recent years, with the progress of biotechnology, molecular targeting drugs such as Cetuximab, Panizumab and new molecular targeting drugs such as Apboxipul, Regolfinib, and Sildenib have been widely used in clinical practice. All the above treatments have certain defects and deficiencies, which can cause serious adverse reactions to the digestive system and blood system^[12]^ or damage the hepatic sinus vessels, resulting in increased perioperative bleeding, thus reducing the surgical resection rate.^[13]^

Traditional Chinese medicine (TCM) is characterized by simplicity, convenience, simplicity, and efficiency, which provides a new therapy pattern. According to a recent study, combined with Western medicine treatment or not, TCM therapies have shown efficacy for CRLM. It can not only assist the human body to restore *qi* and create surgical conditions for some CRLM patients, but also play an important role in reducing side effects from surgery, radiotherapy, and chemotherapy. Through the search of clinical and experimental studies on TCM treatment of CRLM in recent years, it is found that the treasure house of TCM has not been fully tapped in the treatment of CRLM, the research quality is low. To enrich the means of TCM treatment, it should seek more effective and more abundant methods of TCM treatment of CRLM.

Buzhong Tiangan Formula (BTF) is an experience formula in treating CRLM, which has been used for more than 20 years in our team, while there are lacking of evidence on its effective in delaying colorectal liver metastasis (liver depression spleen deficiency type). So, the purpose of this study is to verify the efficacy of BTF in preventing the occurrence of CRLM and to prolong the time phase of CRLM.

## Materials and methods

2

### Study design

2.1

This is a prospective, multicenter randomized controlled trial (RCT) of BTD for delaying colorectal liver metastasis (liver depression spleen deficient type). Included patients are planned to be divided into 2 groups: the treatment group (received basic anti-tumor drugs plus BTD), and the control group (received basic antitumor drugs). The patients are planned to be followed ups for 2 years after 12-week treatments. The flow diagram is shown in Figure 1. This protocol followed the Standard Protocol Items: Recommendations for Interventional Trials (SPIRIT) (Fig. 1).

**Figure 1 F1:**
[figure not shown]
Study flowchart.

### Ethics and registration

2.2

This RCT has been approved by the Human Research Ethics Committee of Shanxi Province Hospital of Traditional Chinese medicine (2021Y-06016) and has been registered under the Chinese Clinical Trial Registry (ChiCTR2100050757). The participants who must sign the informed consent form will be involved, and they can quit this study at any time.

### Patients

2.3

#### Diagnostic basis

2.3.1

The diagnostic criteria for CRC refer to Guidelines for diagnosis and treatment of CRC (2020); The diagnostic criteria of Chinese medicine syndrome type refer to Standard of China Association of Traditional Chinese Medicine Guideline for TCM diagnosis and Treatment of tumor (2008).

#### Inclusion criteria

2.3.2

1.Age >18 years, excepted survival ≥6 months;2.Patients with CRC without liver metastasis (spleen deficiency and liver depression type) that meet the above-mentioned diagnostic criteria of Western medicine and Chinese medicine and have been diagnosed by definite pathology or cytology;3.Those who have not taken TCM and received chemotherapy in the last 1 month;4.No other primary tumors and serious heart, liver, and kidney diseases;5.Those who have the telephone number and address of follow-up, are willing to cooperate with follow-up, have relatively complete medical records, and have signed informed consent.

#### Exclusion criteria

2.3.3

1.Nonprimary CRC with unclear diagnosis;2.Unable or unwilling to receive TCM treatment;3.The patient has developed intestinal obstruction, cannot take medication, needs intravenous high-energy nutrition, or has malabsorption syndrome or other diseases affecting gastrointestinal absorption, or has active peptic ulcer disease.

#### Shedding criteria

2.3.4

1.Poor compliance;2.Serious adverse events, complications, and special physiological changes should not continue to be accepted by researchers;3.Quit voluntarily;4.Misdiagnosed or included by mistake.

### Sample size

2.4

According to the results from a preliminary small sample clinical trial carried out by our team and literatures, the 1-year survival rate was 65% and the median survival period was 17 months in the treatment group, and 55% and 14 months in the control group. The Ebricalc2000 software calculated that 60 cases should be required for each group, with an estimated drop-out rate of 20%, 75 participants should be enrolled in each group.

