### Randomization and blinding

2.5

The included participants will be divided into the treatment group and the control group randomly in a 1:1 ratio. SAS9.3 software will be used for generating random sequences by an independent researcher who will be not involved in the period of treatment and data analysis. The central randomization system (provided by the department of oncology, Shanxi Province Hospital of Traditional Chinese Medicine) will be used and for each center, the clinical investigators will log into the central system by telephone or internet for applying for the randomization number for a new included patient.

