#### Primary outcomes

2.7.1

1.Quality of life of CRC patients: measured by the medical outcomes study item short from health survey (SF-36) which developed by the Medical Outcomes Study and Karnofsky score (KPS). SF-36 is involving 8 aspects including physical functioning, role-physical, bodily pain, general health, vitality, social functioning, role-emotional, and mental health;2.The time of occurrence of liver metastasis, the size of tumor, and the expression of tumor markers in the serum;3.The score of TCM symptom for the type of liver depression spleen deficiency.

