#### Secondary outcomes

2.7.2

1.Overall survival, progression-free survival, or disease-free survival (DFS);2.Tumor microenvironment, measured by vascular endothelial growth factor receptor (VEGFR) and Th1/Th2 in the serum;3.Immune state of the patient, measured by subset of the class of T-cells in the serum.

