### Statistical analysis

2.10

Data analysis setting will follow intent-to-treat (ITT) principles. Data will be statistically analyzed by SPSS 23.0 software. Chi-Squared test will be used for enumeration data, and mean ± standard will be used for measurement data. Drawing survival curves of overall survival, progression-free survival, and DFS will use Kaplan–Meier and the difference between the treatment group and control group will use log-rank. If possible, subgroups analysis will be carried out by the left or right colon, gene status, sex, and age. *P* < .05 will be considered a significant statistical difference.

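### The sample size rests on survival, a secondary outcome; no primary outcome is sized, and 60 per group does not follow from the survival figures given

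*Protocol article*

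**What the plan says.** Section 2.4 (Sample size) gives the inputs as "the 1-year survival rate was 65% and the median survival period was 17 months in the treatment group"; for the comparator arm it assumes 55% at one year with a median of 14 months. From these it concludes that "60 cases should be required for each group, with an estimated drop-out rate of 20%, 75 participants should be enrolled in each group". It does not say which survival endpoint is meant; overall survival is the plain reading.

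Section 2.7.1 (Primary outcomes) lists quality of life by SF-36 and KPS, then "The time of occurrence of liver metastasis, the size of tumor, and the expression of tumor markers in the serum", then the TCM symptom score. Section 2.7.2 (Secondary outcomes) lists "Overall survival, progression-free survival, or disease-free survival (DFS" among the secondary outcomes. Whichever survival endpoint section 2.4 intends, it is therefore not primary.

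Patients must be free of liver metastasis at entry (2.3.2), and the stated purpose is to prevent or delay it (end of the Introduction). Allocation is 1:1 (2.5). Section 2.10 sets the significance level: P "< .05 will be considered a significant statistical difference".

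**The concern.** A sample size justification should tell the reader what the trial can show on its primary outcomes. Here it refers to a different outcome. Medians of 14 and 17 months of survival say nothing about how many patients will develop liver metastasis, how soon, or how far the SF-36, KPS or TCM scores might move.

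If the number also fails to follow from its own inputs, 60 per group is supported neither for the primary outcomes nor for the survival outcome it was drawn from. A non-significant result on metastasis could then be read as evidence against the formula when the trial could not have detected a moderate delay.

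**Working it through.** **Inputs from the article.** One-year survival 65% versus 55%; medians 17 versus 14 months; 60 per group, raised to 75 for 20% drop-out; 1:1 allocation; significance level 0.05; follow-up of 12 weeks plus 2 years, about 2.8 + 24 = 26.8 months.

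**Assumptions.** Two-sided test and 80% power, because the article states neither. z values 1.960 and 0.842; (1.960 + 0.842)² ≈ 7.849.

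**1. The plan's own figure.** The drop-out step is right: 60/(1 − 0.20) = 75. The 60 is not reproduced.

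- *One-year rates.* n per group = [1.960·√(2·0.60·0.40) + 0.842·√(0.65·0.35 + 0.55·0.45)]² / 0.10² ≈ 376. Other settings: 396 with continuity correction, 503 at 90% power, 296 one-sided at 80% power. The smallest variant tried is 296. At 60 per group, power is about 20% (30% one-sided).
- *Medians.* HR = 14/17 = 0.824 under exponential survival. Events = 4 × 7.849 / (ln 0.824)² ≈ 833 (Schoenfeld); 839 by Freedman.
- *HR implied by the one-year rates.* ln 0.65 / ln 0.55 = 0.721, which needs about 293 events.

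**2. Power for survival with 120 patients.** Assume exponential survival and all patients followed to 26.8 months. Expected deaths are 60·(1 − 0.5^(26.8/14)) + 60·(1 − 0.5^(26.8/17)) = 44.1 + 39.9 ≈ 84. Power = Φ(|ln HR|·√84/2 − 1.960):

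- HR 0.824: Φ(0.890 − 1.960) ≈ 14%.
- HR 0.721: Φ(1.502 − 1.960) ≈ 32%.

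The exponential model is only approximate: 65% at one year implies a median of 12·ln 2/(−ln 0.65) = 19.3 months, not 17.

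**3. Time to liver metastasis.** The article gives no event rate, so the control incidence over follow-up, p, is an assumption. The treated incidence is 1 − (1 − p)^HR, and events are n·p + n·[1 − (1 − p)^HR]. Solving |ln HR|·√events/2 = 1.960 + 0.842 for HR:

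| Assumed control incidence | 60 per group: HR (events) | 75 per group: HR (events) |
|---|---|---|
| 20% | 0.24 (15) | 0.28 (20) |
| 35% | 0.36 (30) | 0.40 (38) |
| 50% | 0.44 (46) | 0.48 (59) |

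At 35% and 60 per group, the detectable contrast is 35% versus about 14%. At control incidences of 35% to 50%, power at 60 per group is 9–11% for HR 0.82 and 19–25% for HR 0.70. As a bound, if all 120 patients had the event, the detectable HR would be exp(−2 × 2.802/√120) = 0.60.

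**4. Continuous primary scores.** Detectable standardised difference with 60 per group: 2.802 × √(2/60) ≈ 0.51 SD.

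**The case against.** The article condenses a fuller protocol, so unstated power, sidedness and software settings are no fault in themselves. That stands. But the article does state the basis of its number, and that basis is a non-primary outcome. No standard setting tried brings the requirement near 60.

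The metastasis figures depend on an incidence the article does not give. That also stands, which is why a range is shown. A reader might take the Introduction's statement that "35% of patients treated with curative intent will develop metastatic disease" as a ceiling. It is not one. It concerns metastasis at any site after curative treatment, entry is not restricted to such patients, and the Introduction also says that nearly half of patients present with or develop liver metastasis. Both are proxies. Nor should 35% be applied to both arms together: that gives 42 events among 120 patients and a detectable HR of 0.42, which is too favourable if 35% is the control incidence.

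A reader might also infer that every primary outcome is underpowered. The article does not support that. Quality of life stands first in the primary list, and about 0.5 SD may be adequate for a continuous score. What is missing there is a justification.

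Finally, rewording section 2.4 adds no power. That is true; it makes the stated capability honest.

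**Conclusion.** Wrong as written. Section 2.4 sizes the trial on survival (apparently overall survival), which is secondary, and gives no sizing assumption for any primary outcome. This part rests on the text alone.

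The stated 60 per group does not follow from the survival inputs: the need is roughly six times as many for the one-year rates (376/60 ≈ 6.3), assuming a two-sided 0.05 test with 80% power, and still 296 one-sided. The power of 14% and 32% for survival also assumes exponential survival and complete follow-up to about 27 months.

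For time to liver metastasis, 60 per group can reliably show only a large delay. The detectable HR is 0.24 to 0.44 for assumed control incidences of 20% to 50%, and no better than 0.60 even if every patient has the event. The exact value depends on the assumed incidence; the conclusion does not.

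**What to change.** Keep 150 patients and restate section 2.4:

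- Remove the statement that the survival figures require 60 per group. Name the survival endpoint, call it secondary, and state its low power.
- For time to liver metastasis, state the assumed control incidence over follow-up, the expected events in both arms together, and the HR detectable with 80% power. At 35% control incidence this is about 0.40 with 75 per group (38 events) and about 0.36 with 60 (30 events). Add a range such as 20% to 50%.
- For the SF-36, KPS and TCM scores, state the detectable standardised difference, about 0.5 SD with 60 per group.
- State the significance level, sidedness and power used for each figure.

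The cost is a rewrite of one section, with no added patients. The downside is that the stated detectable effect is less favourable than the present text suggests.

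### Sample size: 60 per group does not follow from the survival figures given for it at P < .05; those figures need about 216 to 595 per group for 80% two-sided power

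*Protocol article*

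**What the plan says.** Section 2.4 (Sample size) of the protocol article draws its planning figures from a small preliminary trial and the literature. For the BTF arm, "the 1-year survival rate was 65% and the median survival period was 17 months in the treatment group"; for the comparator, "55% and 14 months in the control group". From these it concludes: "The Ebricalc2000 software calculated that 60 cases should be required for each group". The figure is then raised for attrition: "with an estimated drop-out rate of 20%, 75 participants should be enrolled in each group".

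Section 2.4 gives no power, sidedness, formula or test. The only significance level is in section 2.10 (Statistical analysis), where P < .05 "will be considered a significant statistical difference". Section 2.10 also names chi-squared for enumeration data, Kaplan–Meier with log-rank for survival, and intention to treat. Section 2.5 has patients "divided into the treatment group and the control group randomly in a 1:1 ratio". Section 2.1 sets the follow-up: "The patients are planned to be followed ups for 2 years after 12-week treatments". Overall survival is a secondary outcome (section 2.7.2).

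**The concern.** The inputs and the output of the calculation are both printed, so it can be checked. A 10-point difference near 60%, or a 3-month difference in medians of 14 and 17 months, is a modest effect, and 60 per group looks far too few to detect it at the 5% level.

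An ethics committee or reader will take 60 per group as the number that gives adequate power for this effect. If it does not, the survival comparison will most likely be non-significant even if BTF works exactly as assumed. There is then a risk that such a result is taken as evidence of no benefit.

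**Working it through.** **Inputs.** 65% vs 55% at 1 year and medians of 17 vs 14 months (section 2.4); alpha 0.05 (section 2.10); 1:1 allocation (section 2.5); 12 weeks plus 2 years, about 26.8 months (section 2.1). *Assumed, because not stated:* 80% power; a two-sided test (one-sided also tried); exponential survival for death counts; every patient followed for the full 26.8 months.

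**1. Attrition step.** 60/(1 − 0.20) = 75. This reproduces, so the problem lies in the 60.

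**2. Chi-squared on the 1-year rates.** With the pooled proportion 0.60,

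n = [z(α)·√(2·0.60·0.40) + z(power)·√(0.65·0.35 + 0.55·0.45)]² / 0.10²

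= [1.960·0.6928 + 0.8416·0.6892]² / 0.01 = 375.6, so 376 per group.

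| Setting, 5% level | n per group |
|---|---|
| Two-sided, 90% power | 503 |
| Two-sided, 80% | 376 |
| One-sided, 80% | 296 |
| Two-sided, 50% | 185 |
| One-sided, 50% | 130 |

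For these rates, a figure near 60 appears only at a setting such as one-sided alpha 0.20 with 60% power (58 per group), which conflicts with P < .05.

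**3. Log-rank on the medians.** Hazard ratio (HR) = 14/17 = 0.8235. By Schoenfeld's formula, deaths = 4(1.960 + 0.8416)² / (ln 0.8235)² = 833. The mean probability of death by 26.8 months is 1 − (2^(−26.8/14) + 2^(−26.8/17))/2 = 0.700, so n = 833/(2·0.700) ≈ 595 per group.

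**4. Log-rank on the HR implied by the 1-year rates.** HR = ln 0.65 / ln 0.55 = 0.7206. Deaths = 293. The mean probability of death by 26.8 months is 1 − (0.65^(26.8/12) + 0.55^(26.8/12))/2 = 0.677, so n ≈ 216 per group. One-sided: 231 deaths, about 171 per group. This is the smallest requirement found at 80% power and 5% alpha, and it is nearly three times 60.

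**5. Power delivered, two-sided 5%.** Chi-squared: Φ{(0.10·√n − 1.960·0.6928)/0.6892}. Log-rank: Φ{½·√deaths·|ln HR| − 1.960}.

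| Comparison | 60 per group | 75 per group |
|---|---|---|
| Log-rank, HR 0.82 | 14% (84 deaths) | 17% (105 deaths) |
| Chi-squared, 65% vs 55% | 20% | 24% |
| Log-rank, HR 0.72 | 31% (81 deaths) | 38% (102 deaths) |

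A one-sided 5% test at 60 per group gives 30% on the 1-year rates and 43% by log-rank at HR 0.72.

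**6. Effect detectable with about 80% power, 60 evaluable per group, two-sided 5%.**
- 1-year rates: 79% vs 55% gives 81% power; 78% vs 55% gives only 77%.
- Log-rank, 14-month control median: at HR 0.52 the probabilities of death by 26.8 months are 0.735 (control) and 0.498 (BTF). Deaths = 60·(0.735 + 0.498) ≈ 74, against 73.4 needed, so power is 80%. The death count has to be recomputed at each HR: at HR 0.54 about 75 deaths are expected and power is 76%.

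**The case against.** **Power and sidedness are unstated, and a condensed article may leave them to the full protocol.** Fair, and their absence is not the point. It does mean that 376 is not a property of the inputs alone: it assumes 80% power, a two-sided test and chi-squared on the 1-year rates. But no setting tried that is compatible with P < .05 and has conventional power comes near 60, so the conclusion does not depend on those choices.

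**The power may be better than the worst figures suggest.** This stands. A reader who looks only at chi-squared on the rates and log-rank on the medians would infer 14–20%. Log-rank is the test planned for survival, and at the HR implied by the 1-year rates it gives about 31%. Under intention to treat with all 75 per group followed, it reaches 38%. The trial is still underpowered for this effect, but the full range should be quoted.

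**The two input pairs might seem to contradict each other.** Under an exponential model the medians imply HR 0.82 and the rates 0.72, and a 17-month median gives 61% at 1 year rather than 65%. The protocol never claims exponential survival. A Weibull curve with shape about 1.37 passes through both BTF figures, and the control pair is almost exactly exponential (a 14-month median gives 55.2%). The documents therefore do not support a charge of inconsistency.

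**Survival is only a secondary outcome.** Correct. Low power for survival does not show that the primary comparisons in section 2.7.1 are underpowered, and nothing here tests that. But survival is the only basis section 2.4 offers for the size, so the statement still has to be right.

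**Conclusion.** The point holds as a failure to reproduce. At the protocol's own 5% level, neither 65% vs 55% nor 17 vs 14 months leads to 60 per group. For 80% two-sided power the requirement is about 216, 376 or 595 per group, depending on test and input pair, roughly 4 to 10 times the stated figure; the most lenient case tried (one-sided log-rank, HR 0.72) needs 171. Two-sided power for the planning effect is about 14% to 31% with 60 evaluable per group, and about 17% to 38% if all 75 are followed.

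The log-rank figures rest on exponential survival and full follow-up of about 27 months; the chi-squared figures do not need the exponential assumption. Two stronger inferences are not supported: that the planning inputs contradict each other, and that the trial fails for its primary outcomes. Nor does any passage say that a null survival result would be read as no effect; that is a risk to guard against.

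**What to change.** Reword section 2.4, keeping 75 per group:

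- Withdraw the statement that 60 per group are required for the quoted survival difference.
- State alpha, sidedness and the power delivered for the planning effect. Two-sided at 5%, that is about 14%, 20% or 31% with 60 evaluable per group (17%, 24% or 38% with all 75), naming the test and input pair for each.
- Give the effect detectable with 80% power from 60 evaluable per group: about 79% vs 55% at 1 year, or HR about 0.52 (about 74 deaths, exponential survival, 14-month control median, about 27 months of follow-up).
- If the hazard ratios of 0.72 and 0.82 are both mentioned, mark the difference as dependent on the exponential model, or leave it out.

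In section 2.10, say that survival, as a secondary outcome, will be reported with a 95% confidence interval and that a non-significant result will not be interpreted as absence of effect.

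The cost is a change of text. No patients, visits or follow-up are added, but the stated power becomes visibly less favourable.

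### The 60 per group in the sample size section does not follow, by any conventional superiority calculation, from the survival figures it is said to rest on

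*Protocol article*

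**What the plan says.** Section 2.4 (Sample size) cites a small preliminary trial and the literature for its effect figures. Control survival is put at 55% with a median of 14 months; for the other arm the text reads "the 1-year survival rate was 65% and the median survival period was 17 months in the treatment group". On the size itself it states: "The Ebricalc2000 software calculated that 60 cases should be required for each group". Allowing for 20% dropout, it then plans to enrol 75 per arm. It gives no significance level, sidedness, power or test for this calculation.

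Other sections supply the remaining inputs. Section 2.5 allocates "randomly in a 1:1 ratio". Section 2.10 sets significance at P below .05 and says of overall, progression-free and disease-free survival that "the difference between the treatment group and control group will use log-rank". Section 2.1 plans 2 years of follow-up after 12 weeks of treatment. Section 2.7.2 lists the survival endpoints as secondary. The primary outcomes in section 2.7.1 are quality of life, the time to liver metastasis (with tumour size and serum markers) and the TCM symptom score.

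**The concern.** The section presents 60 per group as the output of a calculation on the quoted survival figures. A difference of 10 percentage points near 60%, or of 3 months between medians, is modest, and 120 patients is far fewer than such differences usually require. If the number does not follow from its inputs, readers and the ethics committee are told that the trial can detect a survival benefit that it would more often miss than find. The survival comparison would then be interpreted against a claim that the design does not support.

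**Working it through.** **Inputs.** From section 2.4: 65% and 55% at 1 year; medians 17 and 14 months; 60 per group; 20% dropout. From section 2.5: 1:1 allocation. From section 2.10: 5% level and log-rank test. From section 2.1: 12 weeks plus 2 years, about 26.8 months per patient. Assumed, because not stated: two-sided testing (one-sided also tried), 80% power, exponential survival and complete follow-up.

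**The plan's own figure.** The dropout step reproduces: 60/(1 − 0.20) = 75. The 60 does not.

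**Route 1: 1-year rates.** With mean proportion 0.60,

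n = [1.960·√(2·0.60·0.40) + 0.842·√(0.65·0.35 + 0.55·0.45)]² / 0.10² = 376 per group.

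The unpooled formula gives (2.802)²·0.475/0.01 = 373. One-sided 5% gives 296. Even 50% power at one-sided 5% needs 130.

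**Route 2: log-rank, hazard ratio from the 1-year rates.** HR = ln 0.65/ln 0.55 = 0.72.

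Deaths = 4·7.849/(ln 0.7206)² = 292 (one-sided, about 231).

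The expected proportion dying by 26.8 months is 67.7%, so 292/(2·0.677) is about 216 per group.

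**Route 3: log-rank, hazard ratio from the medians.** HR = 14/17 = 0.82.

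Deaths = 4·7.849/(ln 0.8235)² = 833 (one-sided, about 657).

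The expected proportion dying is 70.0%, so about 596 per group.

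In routes 2 and 3 the deaths required exceed the 120 evaluable patients, so longer follow-up could not close the gap.

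**Power at the planned size.** For the log-rank test, power = Φ(½·√D·|ln HR| − z), where D is the expected number of deaths by 26.8 months.

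| Difference tested | 60 per group, two-sided 5% | 75 per group, two-sided 5% | 60 per group, one-sided 5% |
|---|---|---|---|
| 65% vs 55% at 1 year | 20% | 24% | 30% |
| HR 0.72 (about 81 deaths with 60 per group) | 31% | 38% | 43% |
| HR 0.82 (about 84 deaths with 60 per group) | 14% | 17% | 22% |

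If all 120 patients died, two-sided power would still be only 43% (HR 0.72) and 18% (HR 0.82).

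**What 60 per group can detect** (two-sided 5%, 80% power, control median 14 months, 26.8 months). At HR 0.52 about 44 control and 30 treated patients die, 74 in all, and the requirement is 4·7.849/(ln 0.52)² = 73. That corresponds to a treated median of 14/0.52, about 27 months. The death count has to be recomputed for the larger effect: at HR 0.54 only about 75 deaths are expected against 83 needed, and power is about 76%. For the 1-year rates, 55% against 78% gives 77% power and 55% against 79% gives 81%.

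**The case against.** The article condenses a fuller protocol, and error rates may be stated there. That is fair, and their absence is not the point. The point is that no usual choice of them brings either pair of figures to 60.

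Some settings do land near 60. One-sided 20% with 60% power gives 58 per group for the 1-year rates; a non-inferiority test with a 15-point margin gives 60; treating 17 and 14 months as normal means gives 60 if the standard deviation is about 5.9 months. So a reader who infers that 60 cannot be obtained at all goes too far. But section 2.10 uses P below .05, no margin is stated, the introduction aims to verify efficacy, and exponential survival with these medians has standard deviations of 14/ln 2 = 20.2 and 17/ln 2 = 24.5 months. Nothing in the text supports any of these routes.

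The power range is conditional, and this objection stands. The four survival figures do not fit exponential curves exactly: 65% at 1 year implies a median of 19.3 months, not 17. Weibull curves fitted to all four meet near the end of follow-up, and simulated log-rank power is then about 9%. The range of 14% to 31% therefore describes stated scenarios and is not a bound. Section 2.4 also does not say which population its figures describe, so actual deaths among enrolled patients, who have no liver metastasis at entry, may differ.

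Finally, survival is secondary. A reader might infer that the trial is underpowered for its primary outcomes. These calculations do not show that, because the documents give no effect sizes for those outcomes.

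**Conclusion.** The point holds as a failure of the stated calculation. Depending on the pair of figures used, the conventional two-sided requirement is about 216 to 596 per group, roughly 3.6 to 10 times the stated 60. Under two-sided 5%, exponential survival and complete 26.8-month follow-up, 60 evaluable per group would miss the quoted survival differences about 7 to 9 times in 10. Having all 75 per group evaluable, or testing one-sided, raises power but leaves it at 43% or less.

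The finding is confined to survival, which is the sole basis given for the size but a secondary outcome. It does not show that more patients must be enrolled, and the documents do not say that a non-significant result would be reported as no benefit. That is a risk to guard against, not a stated intention.

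**What to change.** Keep 75 per group. In section 2.4, either withdraw the statement that 60 per group is the calculated requirement for these survival figures, or disclose the inputs, test, significance level and power that produced it. The replacement should not supply a rationale, such as feasibility, unless that was in fact the basis.

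Add to section 2.4, with the assumptions named (two-sided 5%, exponential survival, control median 14 months, 26.8 months of follow-up): 60 evaluable per group gives 80% power only for a hazard ratio of about 0.52 (about 74 deaths, treated median about 27 months) or for 55% against about 79% at 1 year; power for the quoted differences is about 14% to 31%; and these figures concern the secondary survival outcomes.

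In section 2.10, add that survival will be reported as a hazard ratio with a 95% confidence interval and that a non-significant log-rank result will not be read as absence of benefit.

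The cost is rewording two sections, with no extra patients. The stated justification becomes less favourable, and the size remains without a stated basis for the primary outcomes.
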